#### Qualitative Analyses

We will engage in content analysis [51] and use interview transcripts to sort descriptions, concepts, and central ideas into potential themes and concerns that occur repeatedly using the scrutiny techniques of repetitions and similarities and differences [52] and link themes to verbatim quotes [53]. Qualitative transcript data will be analyzed using descriptive content methods to identify domains or taxonomies about REACH TBI experiences. Content analysis will allow a priori coding framework derived from previous research literature and interview data to develop the coding scheme [51]. To adequately capture access determinants among participants, a qualitative codebook will be developed using deductive codes generated by construct relevance and inductively from interview data [54], as well as input from SME stakeholders (eg, TBI caregivers and PSC clinicians). Interview transcripts will be coded by the qualitative team using the codebook augmented by our SMEs to assess intervention satisfaction and implementation issues. Additional codes will emerge inductively from the interview data. The coding team will read 1 interview transcript separately and discuss the addition of new codes with examples. This process will continue with subsequent transcripts until no new codes are generated (code saturation) [55]. Intercoder reliability will be established when the coding team reaches at least 80% coding agreement [56]. Intercoder reliability will be routinely monitored to ensure consistency and limit potential drift in coding. Any discrepancies will be discussed and resolved among study staff during weekly meetings to ensure coding and analysis are completed on schedule or earlier. ATLAS.ti (version 22; ATLAS.ti Scientific Software Development GmbH), a qualitative analysis software program, will be used to manage and code interview text using a constant comparative approach. Coded text will be displayed in Excel (Microsoft Corp) spreadsheets to conduct a matrix analysis, a rapid assessment approach, which will be used to develop themes for the overall sample. Comparative matrices enable the identification of the most relevant, shared, and perhaps representative components, thereby enhancing the potential representation of the findings and allowing discernment of the most salient and representative experiences with REACH TBI identified by participants.

### Human Participants Protections and Adverse Events

We do not anticipate any severe adverse events or major psychological, legal, social, or economic risks from study participation. However, we anticipate the following (uncommon) minor risks: (1) participants may experience discomfort or fatigue in answering questions; (2) in the intervention, some of the discussion topics may be upsetting, and (3) if using a landline telephone, there will be no charges for calls from the REACH interventionist, but if using a cellular phone, calls by the REACH interventionist may use cellular minutes, and the participant may incur charges, depending on the user plan.

We will have multiple checks against adverse events. Alerts may be recognized during data collection, outside scheduled contacts, and during intervention sessions. Alerts or adverse event standardized procedures will address suicidal ideation, clinical depression levels, and safety risks. The procedure ensures that any alert is discussed immediately with a supervisor and appropriate action is taken. Alerts identified during data collection will be placed in the participant’s secure shared folder and an email sent to the interventionists and principal investigator (PI). Alerts will be discussed by the interventionist either during the randomization call for waitlist control participants or during the randomization call and session 1 for treatment-arm participants. The procedure ensures that any alert is discussed immediately, and appropriate action taken. For example, for clinical depression levels, we will follow up with the participant who will also be advised to contact their physician or other resource. All alert events will be recorded on the project alert form that includes the event date, whether the event is treatment-related, and the date the event was addressed. Interventionists will address alerts with the caregivers, complete the alert form, upload it to the participant’s secure shared folder, and email the PI that the alert was addressed. If appropriate, the PI will report the event to the IRB. Alerts, adverse events, and referrals will not cause a participant to be dropped from the study. Any contact outside data collection will be documented (time, reason, actions taken, and initiator) on an additional contact tracking form.

To ensure prompt reporting of research-related events, we will follow IRB guidelines. As soon as possible but in all cases within 1 to 5 working days, the PI will report to the IRB any changes to the protocol that were taken to eliminate hazards to a research participant, deviations to protect the physical well-being of a participant in an emergency, and any serious adverse event, related or possibly related to the research regardless of whether the event occurred during the study. Participants will have access to call study personnel and the PI during normal business hours to report concerning effects. A more thorough investigation of adverse effects will be performed as needed. While we do not anticipate serious adverse events that call for emergency care, if emergency care is required during a study visit, study staff will contact emergency services, and study staff will work with the participant to obtain such care. It will be emphasized to participants that they can take a break or discontinue either data collection or the REACH sessions at any time. An individual’s participation in the study will be terminated if the participant wishes to stop their participation in the study or in response to any significant adverse event determined by staff to warrant stopping study treatments. If the V/SM objects to their caregiver participating, this can also be a reason for discontinuation.

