### Data Collections

#### Quantitative Data Collection

Demographic and baseline data will be collected either by telephone or Qualtrics (Qualtrics International Inc) after enrollment and before randomization. Baseline data collection includes validated measures of key TBI caregiver outcomes such as strain, depression, anxiety, self-efficacy, and health care frustration. Follow-up data will be collected at 3 and 6 months from all participants and at 9 months from waitlist control participants using the same validated measures as during the baseline data collection. The study timeline is illustrated in Figure 1.

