#### Primary Quantitative Analyses

The intention-to-treat principle will be applied to all analyses. Once a participant is assigned to a treatment group, they will be included in the group in all analyses even if they end treatment or are lost to follow-up. Parallel analyses will be completed for each outcome. A linear mixed effects model [41] will be used to test the effectiveness of the REACH TBI intervention compared to a waitlist control initially for the primary outcome of caregiver strain. Contrasts will be coded to allow for tests of the mean difference between groups at 6 months postintervention and 3 months postintervention with 3-month measurements as the primary outcome. Each participant’s baseline score on the outcome will be included in the model in addition to a random intercept and fixed effects of treatment, time, and the treatment-by-time interaction. To account for multiple testing, Hochberg’s step-up procedure will be used to control the false discovery rate to .05. All analyses will be completed using the lme4 package [49] in the R statistical software (version 4.4.0; R Core Team).

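### The safety section says adverse events never remove a participant from the study, then ends study participation when an adverse event warrants stopping treatment

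*Protocol article*

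**What the plan says.** Both rules stand in the Protocol article, section Human Participants Protections and Adverse Events.

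- **Rule A**, in the account of the alert procedure: "Alerts, adverse events, and referrals will not cause a participant to be dropped from the study". It carries no qualification by severity.
- **Rule B**, later in the same section: an individual's "participation in the study will be terminated" either at the participant's own wish or "in response to any significant adverse event determined by staff to warrant stopping study treatments".

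Three other statements bear on how these should be read.

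- The sentence just before Rule B tells participants that "they can take a break or discontinue either data collection or the REACH sessions at any time". Sessions and data collection can therefore be stopped separately.
- Primary Quantitative Analyses says of randomized participants that "they will be included in the group in all analyses even if they end treatment or are lost to follow-up". Ending treatment and being lost to follow-up are two different things there as well.
- Quantitative Data Collection says: "Follow-up data will be collected at 3 and 6 months from all participants and at 9 months from waitlist control participants".

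**The concern.** There are two defects.

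1. **Conflict.** For a caregiver with a significant adverse event that staff think should end the sessions, Rule A keeps the person in the study and Rule B takes the person out. Neither rule refers to the other or states an exception.
2. **Treatment and follow-up are merged.** The trigger in Rule B is that *treatment* should stop. The consequence is that *study participation* stops. Elsewhere the protocol keeps these apart.

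What is at stake is outcome data. A caregiver whose participation ends before 3 months leaves only a baseline strain score. The primary model uses that score as a covariate, so the person adds no outcome to the primary 3-month contrast. The intention-to-treat rule fixes the arm in which the person is analysed, but it does not supply the missing measurement.

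Before 3 months only the immediate-intervention arm is receiving REACH, so losses under a rule about stopping treatment would be expected mainly in that arm, and among caregivers who may be doing badly. This is an inference. Alerts can arise in either arm ("Alerts may be recognized during data collection, outside scheduled contacts, and during intervention sessions"), and staff could also end a waitlist caregiver's participation before REACH starts.

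**Working it through.** **The two rules applied to one case.** Take a caregiver in the immediate arm who has a significant adverse event before 3 months, and suppose staff decide the sessions should stop.

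| Provision | What happens to this caregiver |
|---|---|
| Rule A | Stays in the study |
| Rule B | Study participation ends |
| Quantitative Data Collection | Surveys due at 3 and 6 months |
| Primary Quantitative Analyses | Analysed in the assigned arm even though treatment ended |

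Three provisions point to continued follow-up and Rule B points away from it. The protocol does not expressly say that surveys stop after a staff decision. That is simply the literal meaning of ending participation in the study.

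**Rough size.** The protocol gives no adverse-event rate, so the number of losses and the outcome deficit of those lost are assumptions.

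Inputs from Participants, Recruitment, and Sample Size: 55 per group, 10% attrition, Cohen *d* of 0.50, pre-post correlation 0.50, two-sided type I error .05.

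Evaluable per arm: 55 × (1 − 0.10) = 49.5, taken as 50.

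*Shift in the 3-month contrast* = (net losses ÷ 50) × D. Net losses are the excess in one arm. D is the deficit, in SD units, that remains after baseline adjustment among those lost.

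| Net losses | D = 0.5 SD | D = 1 SD |
|---|---|---|
| 0 | 0 | 0 |
| 1 | 0.01 SD (2% of 0.50) | 0.02 SD (4%) |
| 2 | 0.02 SD (4%) | 0.04 SD (8%) |

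One loss in each arm with equal D gives net 0 and a shift of 0.

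*Power.* With baseline as covariate, the residual SD is √(1 − 0.50²) = √0.75 = 0.866. The noncentrality is 0.50 ÷ [0.866 × √(1/n₁ + 1/n₂)], and power is taken from the noncentral t distribution.

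- The design as planned, 50 vs 50: 0.50 ÷ 0.1732 = 2.887, power 0.815. This agrees with the protocol's stated 80%.
- Two losses in one arm, 48 vs 50: 0.50 ÷ 0.1750 = 2.857, power 0.807.
- One loss in each arm, 49 vs 49: 0.50 ÷ 0.1750 = 2.858, power 0.807.

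**The case against.** The best case for the text is that it states a general rule and a narrower exception. Rule A closes an account of the alert procedure and can be read as saying that triggering the procedure does not by itself remove anyone. Rule B needs two more conditions: the event is significant, and staff have decided that treatment should stop. Staff facing such an event would turn to the specific rule. On this reading the only thing missing is a cross-reference.

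That reading is plausible and softens the first defect. It does not dispose of it, because Rule A names adverse events separately from alerts and without limit, and the procedures around it cover suicidal ideation, clinical depression levels and safety risks. It leaves the second defect untouched: even as an exception, Rule B ends study participation for a reason that concerns only treatment.

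Other objections carry weight on size.

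- Loss of the surveys is inferred from the wording and not stated.
- Loss counts, deficit and arm imbalance are all assumed, and the range includes zero.
- The sample size already allows for 10% attrition, and power stays above 80% in the cases shown.
- In the immediate arm, an event after the 3-month survey does not touch the primary time point.
- Before REACH starts, a waitlist caregiver has no study treatment to stop, so Rule B hardly fits that case.

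All of these stand, and they keep the point minor.

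Finally, a condensed article may leave safety operating detail to fuller documents. That would answer a complaint about missing detail. It does not answer a conflict between two printed sentences.

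**Conclusion.** The concern holds as a minor point, with medium confidence. As worded, the two rules cannot both be followed for a caregiver whose significant adverse event leads staff to stop treatment, and the second rule ties leaving the study to stopping treatment against the protocol's own separation of the two.

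The consequence for the analysis is probably very small, since the protocol anticipates no severe adverse events. A shift of 0 to 0.04 SD (0 to 8% of the 0.50 SD design effect) and a fall in power of under one percentage point for two losses illustrate the order of magnitude. They rest on assumed loss counts and deficits and are not estimates. The likely concentration of losses in the immediate arm is an inference, and no direction of bias is established. The case for acting is that staff need one rule to follow and that avoidable loss of outcome data should be avoided.

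**What to change.** Two sentences in Human Participants Protections and Adverse Events.

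- **Replace the adverse-event part of Rule B:** a significant adverse event judged to warrant stopping treatment stops the REACH sessions; the 3- and 6-month surveys, and the 9-month survey in the waitlist arm, continue as scheduled unless the participant declines or staff judge data collection itself unsafe for that participant.
- **Add to Rule A:** adverse events may stop the sessions but do not by themselves end follow-up.

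The exit for unsafe data collection is worth keeping because the protocol recognises that "participants may experience discomfort or fatigue in answering questions". An adverse event could then still end follow-up, but only for a reason that concerns the surveys themselves.

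The cost is the two sentences, the consent form if it repeats the rule (it is not shown), and whatever review the overseeing IRBs require for the change. No assessments are added, because the surveys are already scheduled.

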## Results

This study was funded by the Department of Defense in September 2023. Participant recruitment and data collection are expected to begin in 2024. Once REACH TBI effectiveness is demonstrated, the intervention will need to be spread throughout the VA PSC. Rigorous and systematic implementation planning will start in 2026 to broaden the impact of this clinical trial by rolling out REACH TBI among TBI clinicians across the PSC and sustaining intervention delivery.

## Discussion

### Principal Findings

Presently, there is no formalized or structured intervention for caregivers of V/SMs with TBI at a national level, and the existing services provided to caregivers for this population tend to be spread unevenly throughout the VA PSC. These gaps in services will be bridged by adapting the flagship program of the VA Caregiver Support Program’s National Caregiver Center—the evidence-based REACH intervention—to be responsive and relevant to the needs of caregivers of V/SMs with TBI. This intervention has the potential to serve the caregivers currently supporting the needs of nearly half a million V/SMs with TBI, remediating the adverse strain and mental health effects of caregiving, as well as improving self-efficacy and health care frustration. Supporting caregivers directly impacts V/SMs with TBI: higher caregiver health-related quality of life is associated with better functioning in V/SMs with TBI [57], and better caregiver outcomes directly impact the quality of informal care they can provide [58]. The REACH TBI intervention represents a substantial improvement over the current complete lack of a TBI-tailored, standardized but flexible, and evidence-based telehealth intervention available for caregivers of V/SMs with TBI. Further, the telehealth delivery format of the intervention makes it highly suitable for caregivers in rural or other resource-limited environments. This intervention has the potential to increase resilience within caregiving families [59], sustain gains made in functional recovery through the PSC, and ameliorate the negative impacts of TBI-related disability for caregivers.

We foresee several potential limitations and have proactively developed strategies and alternatives to address these. To ensure fidelity of treatment delivery across multiple interventions, the multiple principal investigators will be highly involved in training and supervision of the interventionists on an ongoing basis including regular meetings among these study team members and multiple checks on the reliability and fidelity of the treatment delivery. To support caregivers’ maximal engagement and retention in the trial, we will design the intervention to be responsive to new or ongoing emotional challenges among the participating caregivers, reasonably flexible to accommodate caregiver schedules and other life stressors or demands, and proactive in developing a structured retention plan. Finally, our team will be highly attuned to the complex needs of the V/SMs with TBI that might arise during the study, including detailed standard operating procedures to address behavioral health crises and referrals to appropriate services to address acute concerns within the VA Health Care System.

The near-term impact of this clinical trial will include multiple knowledge products advancing our options to prevent and treat complications resulting from TBI for V/SMs and their caregivers. The immediate outcome will include a manualized, highly portable intervention that can be delivered broadly by TBI clinicians. The intervention will include a resource companion, the REACH TBI Caregiver Notebook, which is being developed in consultation with subject matter experts in the areas of TBI, Military and Veteran health, and caregiving, as well as people with lived experience as TBI caregivers. This product will contain a wealth of information that will be relevant to caregivers of V/SMs regarding practical aspects of managing TBI, problem-solving, and reducing negative mood or affect. The long-term impact of this study is a standardized, evidence-based approach to supporting caregiving families for V/SMs with TBI throughout the entire PSC. This study will also catalyze a subsequent program of research focused on REACH TBI implementation (via subsequent grant proposals or formal PSC and Caregiver Support Program financial support to the caregiver center), to allow future evaluation of REACH TBI service utilization, cost, outcomes, and implementation. This study will provide a model for working from a CBPR framework to integrate perspectives of caregivers of V/SMs with TBI, clinicians who provide care to V/SMs with TBI, TBI clinical researchers, and PSC administrators in all phases of TBI intervention development and implementation.

Beyond its potential impact on the recovery and rehabilitation of V/SMs with a TBI and the well-being of caregiving military families, REACH TBI could be readily adapted and implemented in civilian health care systems. The modular nature of the training materials, the modifiability of the resource guide, and the digital platform to train a broad range of patient-facing staff throughout health care systems well positions REACH TBI to be used in a dual capacity among civilian populations.

### Conclusions

This protocol will use a CBPR methodology to fill a critical gap in meeting the complex needs of V/SMs with TBI and their caregivers. This protocol will target upstream factors affecting adjustment to TBI as a chronic condition, provide solutions to families and communities to mitigate the negative impacts of TBI on V/SM psychological health and functional outcomes, reach V/SMs and caregivers in resource-limited environments via a telehealth modality, and support the uptake of evidence-based interventions at enterprise scale. By engaging key stakeholders throughout the development, testing, and planning to implement REACH TBI, we expect that the resulting intervention will be highly relevant to the target population, usable to a range of providers in multiple settings, and scalable to disseminate broadly.

## Appendix

Multimedia Appendix 1 Peer review summary statement from the US Department of Defense.

## Abbreviations

CBPR: community-based participatory research
HCD: human-centered design
IRB: Institutional Review Board
OEF: Operation Enduring Freedom
OIF: Operation Iraqi Freedom
PI: principal investigator
PROMIS: Patient-Reported Outcomes Measurement Information System
PSC: Polytrauma System of Care
REACH: Resources for Enhancing All Caregivers’ Health
SME: subject matter expert
TBI: traumatic brain injury
USF: University of South Florida
UVA: University of Virginia
V/SM: Veterans and Service Members
VA: Veterans Affairs
